##### Interim analysis

The anticipated trial recruitment duration is 2 years and it is therefore unlikely that sufficient data on the primary endpoint, either for efficacy or futility, will be available to close the trial early, on that basis alone. A close monitoring approach will be adopted to identify loco-regional recurrences (LRR), which will be reported in an expedited fashion by the treating centre. The number of LRR from the total number of patients who commenced trial treatment at that point will be tabulated by treatment group along with a p-value from Fisher’s exact test. The Independent Data Monitoring Committee (IDMC) will use this as guidance together with other emerging trial data to advise on any early cessation of the trial.

#### Quality assurance (QA)

Centres taking part in the trial will be required to successfully to complete the comprehensive Radiotherapy Trials Quality Assurance Group (RTTQA) IMRT credentialing programme in order to be approved to enter patients. This consists of pre-trial contouring and planning benchmark cases exercises together with prospective case reviews for at least the first 2 recruited patients in each centre [41]. A streamlining process for contouring, aiming to minimise QA repetition, exists for centres that have participated in other IMRT Head and Neck trials.

#### Trial organisation

The DARS trial was developed through a multidisciplinary collaboration between the ICR-CTSU and the Head and Neck Units of Royal Marsden Hospital NHS Foundation Trust (RMH), University Hospital Bristol, Norfolk and Norwich University Hospital NHS Trust; Division of Radiotherapy and Imaging of the Institute of Cancer Research (ICR); Speech and Language Therapy (SLT) Departments of RMH, City Hospitals Sunderland NHS Foundation Trust; Department of Physics of RMH and RTTQA. ICR-CTSU will have overall responsibility for trial co-ordination, data collation, central statistical monitoring of data and all interim analysis. A Trial Management Group will be responsible for the day to day running of the trial. The trial will be overseen by an independent Trial Steering Committee. An IDMC will regularly review emerging safety and efficacy data in confidence. The trial is sponsored by RMH and conducted in accordance with the Principles of Good Clinical Practice. This study is included on the National Institute for Health Research portfolio (NIHR number 19934).

## Discussion

The DARS trial is, to the best of our knowledge, the first RCT aiming to demonstrate that reducing the radiation dose to critical swallowing structures can safely improve long- term swallowing function and quality of life. The DARS trial design represents the efforts of a successful collaboration between UK H&N oncologists, physicists, clinical trialists, and SLTs, particularly within the context of a H&N primary CRT trial. Additionally, the association between clinicians and SLTs, both in DARS and the currently recruiting PATHOS trial, has huge potential for the future integration of routine swallowing outcome measures into UK clinical practice for patients with HNC. The trial methodology reflects the necessity to minimise confounding factors that might affect the robustness of its final results. Excluding patients with pre-existing dysphagia ensures that any post- treatment swallowing dysfunction is as a result of (chemo)-radiation treatment alone. Likewise, patients with posterior pharyngeal wall tumours are ineligible for the trial as any meaningful sparing of the PCM is unlikely to be achievable. By being selective in our approach, the trial is better equipped to determine the effectiveness of Do-IMRT across a homogeneous group of pharyngeal cancer patients. Defining the most accurate time point for long-term dysphagia remains controversial within the context of a clinical trial. Swallow sparing studies have so far adopted various time points ranging from 3 to 12 months following completion of treatment [4, 28, 36, 42]. While 3 months is clearly too early to assess long-term functional outcomes, patterns of swallowing function can change between 6 and 12 months with stabilisation thereafter [4, 43], suggesting that the 12- month timeline from treatment completion is more likely to be predictive of subsequent dysphagia.

The DARS trial recognises the importance of a comprehensive assessment for evaluating swallowing by including a multidimensional, longitudinal panel of functional outcome measures integrating instrumental, clinician- rated and patient- reported scales. The dashboard of swallowing measures adopted in DARS was developed in partnership with SLT leads from the PATHOS trial and should help the standardisation of future swallow outcome assessment and reporting. The MDADI composite score, the primary endpoint of DARS, is generated from a feasible and validated patient- reported swallow- specific questionnaire incorporating information from a patient’s physical, functional and emotional level at various recovery time points. Increasingly, it is being adopted as functional outcome tool for a number of head and neck cancer trials [44, 45].

The Do-IMRT is an adaptation of the planning methodology used by Feng et al. in that it will strive to spare the part of the pharyngeal constrictors lying in the elective target volume CTV_5400 rather than the medial RPN alone (Fig. 2) [46]. A theoretical risk of increased recurrence in the spared tissue exists with this approach. It is noteworthy that similar concerns were raised with the landmark parotid- sparing IMRT trial (PARSPORT), but these were proven to be unfounded when the data were analysed [19]. Furthermore, it is well established that the majority of the local recurrences following primary radiation- based treatment are in the immediate vicinity of the primary tumour site (GTV + 1 cm). Importantly, there will be no compromise of target coverage in this volume with Do-IMRT [47–50]. Therefore, the risk of recurrence in the spared tissue is perceived to be minimal. Nevertheless, the IDMC will closely monitor loco-regional recurrence rates and advise on early stopping of the trial if this is deemed necessary. Mean doses to the constrictors above 50 Gy have previously been shown to be associated with the risk of long-term dysphagia [18, 51], and have consequently been incorporated as the dosimetric constraint for the PCM within the study.

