#### Patient population

Patients should satisfy all the inclusion criteria and meet none of the exclusion criteria specified in Table 1 to be eligible for the trial. In brief, patients will have biopsy proven, pharyngeal cancers that will be treated with bilateral neck irradiation. The use of both prophylactic and reactive feeding tube insertions is acceptable, though patients would be encouraged to keep swallowing (even if very limited amounts) for the duration of treatment.

**Table 1 Tab1:** Inclusion and exclusion criteria for patient recruitment in the DARS trial

ᅟ	ᅟ
Inclusion Criteria:	
• Aged 18 or above;	
• Any patient undergoing radiotherapy for HNC in the oropharynx or hypopharynx. Patients with tumour at other sites where radical radiotherapy dose is to be delivered to the pharyngeal constrictors may also be eligible;	
• Stage T1-4, N0-3, M0 disease; this will be mostly histologically confirmed squamous cell carcinoma but other histological types may be eligible;	
• Radiotherapy with concomitant chemotherapy (unless contraindicated) is the planned treatment;	
• Creatinine clearance (≥50 mL/min prior to starting chemotherapy); not applicable for patients receiving radiotherapy alone;	
• WHO performance status 0 or 1;	
• Available to attend long term follow- up;	
• Adequate cognitive ability to complete the MD Anderson Dysphagia Inventory (MDADI), University of Washington Quality of Life (UW-QoL) v.04 questionnaire and Performance Status Scale for Head & Neck Cancer (PSS-HN) assessments;	
• Written informed consent.	
Exclusion Criteria:	
• Documented evidence of pre-existing swallowing dysfunction (not related to HNC);	
• Previous radiotherapy to the head and neck region;	
• Posterior pharyngeal wall, post- cricoid and retropharyngeal lymph node involvement;	
• Lateralised tumours, requiring unilateral irradiation	
• Major head and neck surgery (excluding biopsies/tonsillectomy);	
• Current/previous tracheostomy placement;	
• Previous or concurrent illness, which in the investigator’s opinion would interfere with completion of therapy, trial assessments or follow-up;	
• Any invasive malignancy within previous 2 years (other than non-melanomatous skin carcinoma or cervical carcinoma in situ).	

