#### Study objectives and endpoints

The primary objective of the DARS trial is to determine whether reducing the radiation dose to DARS using Do-IMRT, improves swallowing function compared to S-IMRT in pharyngeal cancer patients treated with radical chemoradiation or radiation alone. The impact of the dosimetric sparing achieved with Do-IMRT on late swallowing function will be evaluated by a patient-reported outcome (PRO) using the MDADI. The difference in the mean MDADI composite score at 12 months after treatment completion between randomised treatment groups forms the primary endpoint of the trial.

Secondary objectives are to:Investigate the longitudinal pattern of patient-reported swallowing function up to 2 years post- radiotherapy treatment using the MDADI;Investigate the impact of using Do-IMRT on(i)normalcy of diet and public eating using the PSS-HN scale;(ii)swallowing performance using the 100 mL Water Swallow Test and VF examination (subset of centres only);(iii)acute and late toxicity(iv)duration of feeding tube use;
Assess patient-reported QoL and priority concerns using the UW-QoL questionnaire (v.04);Compare cancer- related outcomes according to radiotherapy technique used, including resection rates, location and timing of loco-regional recurrence and overall survival.

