#### Assessments

##### Toxicity and response assessments

NCI CTCAE v4.0 will be used to assess acute toxicity data that will be collected weekly during radiotherapy, and at week 1–4 and 8 after treatment completion. Late toxicity will be scored using both NCI CTCAE v4.0 and LENT SOMA scoring systems. Clinical assessments will be made at 6 weeks, and 6, 12, 18 and 24 months after completion of treatment as a minimum. Additional investigations will be requested if clinically indicated. Imaging response will be carried out at 3 months after radiotherapy and reported as per RECIST criteria v1.1. Patients found to have persistent cervical lymphadenopathy will proceed to neck dissection. Late toxicity and survival data will be collected at 3, 6, 12, 18 and 24 months post- treatment, after which routine follow up data will be collected annually for up to 5 years.

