##### Swallowing assessments

A panel of subjective and objective swallowing outcome measures (Table 2) will assess swallow function at regular intervals.

**Table 2 Tab2:** Functional measures and endpoints

Time point	Study	Domain	Endpoint
Baseline, 3, 6, 12, 18 and 24 months	MDADI	Swallowing related QoL	Composite (total), global, emotional, functional and physical subscale scores
Baseline, 3, 6, 12, 18 and 24 months	WST	Swallow Performance	Swallow capacity, Swallow volume
Baseline, 12 and 24 months	VF^a^	Airway protection	Penetration Aspiration Scale [52]
Baseline, 12 and 24 months	VF^a^	Physiology	MBSImp
Baseline, 12 and 24 months	VF^a^	Pharyngeal dysphagia grade	DIGEST grade [53]
Baseline, 3, 6, 12, 18 and 24 months	PSS-HN	Functional Performance Status	Normalcy of diet, eating in public, understandability of speech scores
Baseline, 3, 6, 12, 18 and 24 months	UW-Qol v.04	HR-QoL	Composite scores of physical and social-emotional functioning are derived from 12 domains. Patients can also highlight up to 3 priority concerns from the previous 7 days

Abbreviations: *WST* Water Swallowing Test, *DIGEST* Dynamic Imaging Grade of Swallowing Toxicity, *MBSImp* Modified Barium Swallow Impairment Profile

^a^Subset of centres only

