##### Statistical analysis

The primary endpoint will be compared between the two groups using a two-sample *t*-test or non-parametric Mann–Whitney test, depending on distribution of the composite scores. The primary analysis will be by intention-to-treat, including all patients with 12 month MDADI data. A p-value of <0.05 will be considered statistically significant. Analysis of covariance (ANCOVA) will be used to investigate other patient and clinical factors that could be associated with change in MDADI composite score from baseline to 12 months post- treatment. Chi-squared or Fisher’s exact test will be used to compare patients in both groups with deterioration of 10 points or more in the MDADI composite score.

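### The Discussion says the exclusions make (chemo)radiation the only cause of post-treatment dysphagia, but Table 1 admits patients with tumour-related dysphagia; the randomised comparison is unaffected, and the supporting 10-point comparison should adjust for baseline MDADI

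*Protocol article*

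**What the plan says.** All references are to the protocol article.

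- **Discussion.** As an example of limiting confounding, it says: "Excluding patients with pre-existing dysphagia ensures that any post- treatment swallowing dysfunction is as a result of (chemo)-radiation treatment alone".
- **Table 1 (Patient population).** The matching exclusion reads "Documented evidence of pre-existing swallowing dysfunction (not related to HNC", and the parenthesis closes there. Eligible disease is "Stage T1-4, N0-3, M0 disease".
- **Toxicity and response assessments.** "Patients found to have persistent cervical lymphadenopathy will proceed to neck dissection".
- **Study objectives and endpoints.** "The difference in the mean MDADI composite score at 12 months after treatment completion between randomised treatment groups forms the primary endpoint".
- **Statistical analysis.** The primary test is a two-sample t-test or Mann-Whitney test on everyone with a 12-month MDADI. ANCOVA looks for other factors "associated with change in MDADI composite score from baseline to 12 months post- treatment". A chi-squared or Fisher's exact test will then "compare patients in both groups with deterioration of 10 points or more in the MDADI composite score". No reference time is given for the deterioration. Baseline is implied by the preceding sentence and by Table 2, which schedules the MDADI at "Baseline, 3, 6, 12, 18 and 24 months".

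**The concern.** The Discussion describes a trial population that differs from the one Table 1 admits, and draws a causal conclusion from the difference. A patient whose pharyngeal tumour already makes swallowing difficult passes the exclusion. For that patient, the change from baseline to 12 months is a net figure: recovery as the tumour clears, less damage from treatment. Two things follow.

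1. A reader who trusts the sentence would take all 12-month dysfunction as caused by radiation. The eligibility rules do not support that.
2. A fixed 10-point fall means different things at different starting points. It can miss real treatment damage in a patient who started low because of the tumour.

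**Working it through.** **Step 1: set the passages side by side.** The Discussion claim needs two things: nobody enters with dysphagia, and nothing but (chemo)radiation impairs swallowing afterwards. The first fails because Table 1 limits its exclusion to dysfunction unrelated to the cancer, and no other criterion removes tumour-related dysphagia as such while T1 to T4 primaries are eligible. The second fails because neck dissection may follow radiotherapy and because loco-regional recurrence is expected and monitored. Patients with either event who return a 12-month MDADI are in the primary analysis.

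**Step 2: the plan's own figure.** The Sample size section gives SD 13.8, difference 10, two-sided 5% and 90% power. n per arm = 2(1.960 + 1.282)² × 13.8² / 10² = 40.02, rounded up to 41, as stated. Exact t-test power at 41 per arm is 0.900. Allowing for 20% drop-out, 82 / 0.8 = 102.5 against the stated 102, which is immaterial. This calculation uses the 12-month level only, so Step 1 does not touch it.

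**Step 3: can the effect on the 10-point comparison be sized?** The documents give no baseline MDADI, no mean loss and no share of patients with tumour-related dysphagia. What follows is illustration on assumed inputs. Take the SD of change as 13.8 (borrowed from the 12-month score), a mean radiation loss L in each arm, a 10-point arm difference, and a gain g from tumour clearance in affected patients:

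P(fall ≥ 10) = Φ((L − g − 10) / 13.8)

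For L = 15 and g = 0 this is Φ(5/13.8) = 64.1%. For L = 5 it is Φ(−5/13.8) = 35.9%. The difference is 28.3 points. Rates below are S-IMRT vs Do-IMRT, with the difference in points.

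| Gain g | Losses 15 vs 5 | Losses 25 vs 15 |
|---|---|---|
| 0 | 64% vs 36% (28.3) | 86% vs 64% (22.0) |
| 5 | 50% vs 23% (26.6) | 77% vs 50% (26.6) |
| 10 | 36% vs 14% (22.0) | 64% vs 36% (28.3) |
| 15 | 23% vs 7% (16.1) | 50% vs 23% (26.6) |

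With losses of 15 and 5, relief narrows the contrast. With 25 and 15, it widens it. The difference is largest when the 10-point cut lies midway between the two arms' mean net losses. Losses of 15 and 5 start exactly there, so any shift must reduce it.

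**Step 4: only some patients are affected.** With losses 15 vs 5 and 20% affected, the difference is 0.8 × 28.3 + 0.2 × (difference at g). This gives 27.9, 27.0 and 25.8 points for g = 5, 10 and 15.

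A second scheme assumes an untroubled baseline of 90 and 12-month means of 72 and 82 whatever the baseline. With no affected patients the rates are Φ(8/13.8) = 72% vs Φ(−2/13.8) = 44%, a difference of 27.7 points. If 20% start 10 points lower, the difference is 27.1. If 50% start 20 points lower, it is 20.7.

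**Step 5: does adjustment help?** In simulation at 41 per arm under the second scheme, with a baseline cut that separates the affected patients perfectly, a stratified test changes power from about 73% to 72% in the mild case (20% affected, 10 points) and from about 50% to 61% in the heavy case (50% affected, 20 points). A real cut would separate them less cleanly, so the heavy-case gain is a best case.

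**The case against.** The best defence is that the sentence is discussion prose on which no analysis rests. The effect of Do-IMRT is identified by randomisation, minimised on tumour site and stage among other factors. Target outlining precedes randomisation, and patients and speech and language therapists are blinded. Tumour-related dysphagia is a baseline characteristic, balanced in expectation. All of this stands.

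A reader might infer that tumour relief shrinks the arm difference and could make an effective technique look useless. The documents do not support that: Step 3 shows the direction reversing with the assumed losses, and even the worst case there leaves 16 points. A reader might also infer that the plan presents the 10-point rate as radiation-induced dysphagia. It does not; it only compares arms, and the comparison is not among the listed primary or secondary endpoints.

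Recurrence and surgery are not ignored either. Resection rates and the location and timing of recurrence are compared under the secondary objectives, and recurrence is among the stated reasons for drop-out. Net change is also a legitimate target for a question about patient-reported swallowing.

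Finally, adjusting for baseline cannot identify the cause of a low baseline score. This is true and limits what the remedy can claim. None of these arguments makes the word 'alone' correct.

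**Conclusion.** The point holds as a false statement of a design property, established from the text without any assumption: the exclusion in Table 1 is narrower than the Discussion says, and other causes of dysfunction remain possible after treatment.

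It does not extend to the trial's main inference. The randomised arm comparison, the primary 12-month MDADI test and the sample size are unaffected, and reading the point as bias between arms would be wrong.

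For the supporting 10-point comparison, the finding is that it measures net change from mixed baselines without adjustment. Any effect on the arm difference depends on unknown baselines, losses and prevalence, so neither its sign nor its size can be stated. The illustrations assume normal changes with SD 13.8 and a 10-point arm effect.

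**What to change.** 1. **Discussion.** Reword the sentence to say that only swallowing dysfunction unrelated to the cancer is excluded; that 12-month dysfunction cannot be attributed to (chemo)radiation alone, since tumour-related dysphagia at entry, recurrence and neck dissection may contribute; and that the effect of Do-IMRT rests on the randomised comparison.
2. **Statistical analysis.** Replace the unadjusted chi-squared or Fisher comparison of 10-point deterioration with one adjusted for baseline MDADI. Examples are a Cochran-Mantel-Haenszel test over a pre-set baseline cut, or logistic regression with baseline as a covariate.

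The cost is small: two edits and a slightly longer analysis on data already collected, with no change to eligibility, treatment or sample size. The price is a less clean attribution claim. In mild cases adjustment is about neutral for power. In all cases it improves precision at most and does not separate tumour relief from radiation damage.

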**Fig. 2 Fig2:**
[figure not shown]
Tyler et al. [46] PTV_5400 (blue) dose distribution in (**a**) S- IMRT arm and (**b**) Do-IMRT, demonstrating sparing of dose to Plan SMPCM (yellow)

In conclusion, reducing the risk of late dysphagia in pharyngeal cancers is vital to improve long-term HR-QoL. An increased understanding of the clinical and dosimetric relationship between the swallowing structures and radiotherapy- related dysphagia, together with the availability of novel IMRT techniques, makes it an optimal time to run the DARS trial. The trial is aiming to address the limitations of previous studies aiming to minimise dysphagia by testing Do-IMRT in a randomised study, crucially incorporating a multidimensional approach to swallowing assessment.

## Abbreviations

CRT: Chemoradiation
CRUK: Cancer Research UK
CTV: Clinical target volume
DARS: Dysphagia/aspiration at risk structures
DIGEST: Dynamic Imaging Grade of Swallowing Toxicity
Do-IMRT: Dysphagia-optimised intensity-modulated radiotherapy
FEES: Fibreoptic endoscopic evaluation of swallowing
GTV: Gross tumour volume
HPV: Human papillomavirus
HR-QoL: Health-related quality of life
ICR-CTSU: Institute of Cancer Research Clinical Trials Statistics Unit
IDMC: Independent Data Monitoring Committee
LRR: Locoregional recurrence
MDADI: MD Anderson Dysphagia Inventory
NIHR: National Institute for Health Research
NTCP: Normal tissue complication probability
OAR: Organs at risk
PATHOS: Post-operative adjuvant treatment for HPV positive tumours
PCM: Pharyngeal constrictor muscles
PSS-HN: Performance status scale-head and neck
PTV: Planning target volume
QA: Quality Assurance
RCT: Randomised controlled trial
RMH: Royal Marsden Hospital
RPN: Retropharyngeal lymph nodes
RTTQA: Radiotherapy Trials Quality Assurance
SGL: Glottic and supraglottic larynx
S-IMRT: Standard intensity-modulated radiotherapy
SLT: Speech and Language Therapist
UW-QoL: University of Washington Quality of Life Questionnaire
VF: Videofluoroscopy
WST: Water swallowing test
